#### Data collection

The demographic characteristics will be collected by the research assistants at the recruitment. The primary and secondary outcome data will be collected by the outcome assessors at baseline and at the end of the intervention. All data collection in this study will be performed using standardized procedures, and the outcome assessors will receive standard training on how to measure all outcomes to ensure equal testing conditions for all participants.

To promote participant retention and the provision of complete outcome data from all participants, a total incentive of up to 200 RMB per individual as compensation for their time participating in the study will be provided to all participants. The incentive will be delivered using the way of WeChat draw via WeChat after completion of the final assessment following the 12-week intervention.

#### Data management

The outcome assessors will be responsible for filling in the printed case report form (p-CRF) when they measure the primary and secondary outcomes at each timeline. The research assistants will be responsible for checking the integrity of the completed p-CRF and for timely inputting of the collected data into the EpiData Manager, a free data management software. The project manager will be responsible for initial data cleaning, identifying, and coding and for converting the data into the proper format for analysis.

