### Randomization, allocation, and blinding

The random allocation sequence will be produced by an independent statistician via the PLAN sentences of the statistical software SAS 9.1. The random allocation sequence will be managed by an assigned project manager who will not take part in the participants’ recruitment, and it will be concealed from those research assistants who will be responsible for recruitment or outcome assessment. After signing the informed consent and undergoing baseline assessment of primary and secondary outcome measures, the eligible participants will receive their information of allocation result via WeChat. They will be allocated randomly into either the Baduanjin exercise group or the control group.

Although both the participants and exercise coaches cannot be blinded in this trial, we will blind the outcome assessors and statistics analyzers by the following procedures. Participants’ outcomes will be measured by two special investigators who are not involved in the allocation and exercise intervention. Before the outcome measurement starts, participants, exercise coaches, and the related research assistants will be told not to reveal any information about the allocation. The statistical analysis will be performed by a statistician who does not participate in the implementation of the trial, and the allocation information of the groups will be concealed by a blind code. The blind code will be disclosed when the statistical analysis is completed.

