There are some potential limitations to this study. First, it is difficult to monitor the additional physical activity of participants during the study duration. Although all participants will be required to record their daily physical activity or exercise information by using a step counter in their phone, this is not accurate enough to measure their daily activity intensity. Second, due to unexpected accidents such as training time conflicts with other commitments and bad weather, individual adherence to the Baduanjin exercise regimen in the Baduanjin exercise group may be another issue which can impact the study results. Furthermore, blinding of participants is impossible in this trial, because of the nature of the exercise intervention. However, we will make every effort to ensure that outcome assessors, data managers, and statisticians are unaware of the treatment allocations.

Altogether, the results of this trial may provide evidence of whether regular Baduanjin training can improve the health-related physical fitness of college students in China.

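### The project manager holds the allocation sequence and also cleans and codes the data, which conflicts with the stated effort to keep data managers unaware of allocation

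*Protocol article*

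**What the plan says.** Three places in the protocol article bear on this.

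- **Randomization, allocation, and blinding.** "The random allocation sequence will be managed by an assigned project manager". This person takes no part in recruitment. As for concealment, "it will be concealed from those research assistants who will be responsible for recruitment or outcome assessment"; the project manager is not among those from whom the sequence is hidden. The blinding procedures in this section are for the outcome assessors and the statistical analysts. A blind code hides the groups during the statistical analysis and is opened when that analysis is complete.
- **Data management.** Outcome assessors fill in the paper case report forms, and research assistants check and enter them. Then "The project manager will be responsible for initial data cleaning, identifying, and coding". The sentence goes on to make the same role responsible "for converting the data into the proper format for analysis".
- **Discussion, limitations paragraph.** After conceding that participants cannot be blinded, the article says that every effort will be made so that "outcome assessors, data managers, and statisticians are unaware of the treatment allocations".

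**The concern.** Neither participants nor coaches can be blinded, and most components of the primary composite depend on effort (runs, jump, pull-ups or sit-ups, vital capacity). Protection against bias therefore rests on masked measurement, masked data handling and masked analysis. The article describes procedures for the first and the last. For the step between them it names the one role that manages the allocation sequence.

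Cleaning and coding involve judgement: which value to query, what to do with an implausible or illegible entry, how to code it. If the person deciding can look up the arm, those judgements can differ by arm, even without intent, before the blinded statistician receives the file. A reader who relies on the Discussion would credit the trial with a safeguard that the Methods do not provide.

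**Working it through.** The plan gives no figure on this point and no arithmetic applies. The check is to set the role assignments side by side.

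| Step | Who does it | Masked to allocation, according to the article? |
|---|---|---|
| Holding the allocation sequence | Project manager | No, by function |
| Measuring outcomes and completing the paper form | Outcome assessors | Yes, procedures described |
| Checking and entering forms | Research assistants | Unclear |
| Cleaning, coding, preparing the analysis file | Project manager | Named only in general terms in the Discussion, as data managers; no procedure described |
| Statistical analysis | Statistician outside trial conduct | Yes, blind code |

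1. *Is it one role?* The randomization section speaks of an assigned project manager. The Data management and Safety measurements sections speak of the project manager. No second one is mentioned, so a single role is the natural reading.
2. *Is the project manager a data manager in the sense of the Discussion?* The term is not defined. After form completion by the assessors, the Data management section describes only two data-handling roles: research assistants for checking and entry, and the project manager for cleaning, coding and conversion. A reading of data managers that leaves out the second is hard to sustain.
3. *Does the blind code cover the cleaning step?* It is described in connection with the statistician's analysis. Cleaning comes earlier and is done by the person who manages the sequence that such a code would hide.
4. *Is there another barrier?* The article does not say that the project manager's list is sealed, that cleaning is done on a file without group, or that cleaning ends before the project manager has access to the list. The sequence is in use from the first allocation onwards, before any 12-week data exist.

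The role assignments in the Methods therefore defeat the effort announced in the Discussion, at the cleaning and coding step.

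**The case against.** The strongest reply has four parts.

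- *The Discussion states an aim, not a fact.* This is right: the sentence promises effort and sits among the limitations, and the Methods commit only to masking assessors and analysts. But giving the list and the cleaning to one role undoes that effort by design, so a conflict remains even on the weaker wording.
- *Safeguards exist.* Assessors outside the intervention measure the outcomes and complete the forms, other people enter the data, and the analyst is masked. Paper records therefore exist against which a change made in cleaning could be checked. This stands and limits the seriousness. It allows later detection but does not mask the decisions.
- *A condensed article leaves data-handling detail to the full protocol.* This is true of change logs and file structure. The point here rests on what the article states, namely who does what.
- *The article gives the project manager no authority to exclude values.* This is correct. It speaks of initial cleaning, identifying and coding, and all randomized participants stay in the analysis. Nothing further should be read into those words, such as a formal outlier review.

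A reader might infer two stronger things that the article does not support.

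- *That a few altered readings would change the result.* In Table 2, below 60 points, one 0.2 s row of the 50-m run is worth 10 item points; at a weight of 20% that is 10 × 0.20 = 2 composite points for one participant. With 120 students at 1:1 there are 60 per arm, so one such shift moves an arm mean by 2/60 ≈ 0.03 points. A few shifts would not matter against either reading of the target difference of 5.0% (5 points, or 5.0% of the mean of 55 = 2.75 points).
- *That the research assistants who enter data know the arms.* The article says that "participants, exercise coaches, and the related research assistants will be told not to reveal any information about the allocation", which suggests that some assistants know. It also says "The research assistants will be responsible for checking the integrity of the completed p-CRF". It does not say whether these are the same people, so this stays unclear.

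**Conclusion.** The point holds as a conflict of roles on a blinding safeguard. As written, the project manager both manages the allocation sequence and cleans, codes and prepares the data, while the Discussion presents data managers as people whom the team will try to keep unaware of allocation. The result is an open and avoidable route by which knowledge of the arm could enter the data before masked analysis. It is not evidence that bias occurs, and its size cannot be estimated from the article. No sample-size or power figure changes.

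The conclusion rests on two readings: that the project manager is one role throughout, and that whoever cleans and codes the data counts as a data manager. Both are the natural readings, but neither is spelled out. The matter should be corrected; it does not undermine the design as a whole.

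**What to change.** Give data cleaning, coding and conversion of raw results to points to an existing team member who has no access to the sequence, for example the blinded statistician. The article does not say whether the statistician who generates the sequence is also the one who analyses the data; if so, someone else should do the cleaning. The work should be done on a file without the group variable, with every change logged against the paper form, and the file locked before the coded group is merged. Then bring the randomization section, the Data management section and the Discussion into agreement, and state whether the research assistants who check and enter forms know the allocation.

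If the roles cannot be separated, remove data managers from the blinding statement in the Discussion, so that the article does not claim a protection it lacks.

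The cost is one reassigned task and a few changed sentences, with no new staff. The Trial status section reports recruitment complete on April 30, 2019, so changing custody of the list during enrolment would come too late. It expects trial procedures to run to the end of October 2019, so on that timetable final cleaning could still be moved.

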### Statistical analysis

Analysis of data in this trial will be performed by a statistician who is not involved in the trial. In descriptive analysis of the sample, continuous variables will be expressed by using the mean and standard deviation for normal distributions, and the median and interquartile range for non-normal distributions. Normality will be tested using the Kolmogorov–Smirnov test. Appropriate transformations will be applied in cases of non-normal distribution. Categorical variables will be expressed as proportions with their standard error.

Baseline characteristics between groups will be compared using the *t* test or Mann–Whitney test for continuous variables and Pearson’s χ-squared or Fisher’s exact test for categorical variables. If incomparability appears, the inequality factors will be treated as confounding variables in the final efficacy analysis.

For comparison of primary and secondary outcomes between groups, a *t* test or non-parametric tests will be used for continuous data, and Pearson’s χ-squared or Fisher’s exact test for categorical data at baseline and after intervention; the between-group differences (treatment effects) will be analyzed by using mixed linear models with restricted maximum likelihood using the group-by-time interaction terms. Analysis of the outcomes will be performed on the basis of the intention-to-treat (ITT) population. All participants who have been randomized will be included in the final analysis irrespective of compliance or withdrawal from the program. Full information maximum likelihood estimation will be employed for missing data.

AEs will be listed and analyzed using a χ-squared test or Fisher’s exact test. Severe AEs will be listed and described in detail.

All data will be analyzed with SPSS 21.0 (IBM, Chicago, IL, USA) software packages. Statistical significance is defined as a two-sided *P* value of < 0.05.

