### Study design

This study is a randomized, parallel-group controlled trial to evaluate the effectiveness of a Baduanjin exercise intervention on the physical fitness of college students. A total of 120 eligible college students from the Shanghai University of Medicine and Health Sciences (SUMHS) will be recruited and randomly allocated to either the Baduanjin exercise group or the control group at a ratio of 1:1. Participants in the Baduanjin exercise group will receive a 12-week supervised Baduanjin exercise training intervention with a frequency of 1 h each day and 4 days per week, while those in the control group will not receive any specific exercise intervention and will be informed to maintain their original lifestyle for 12 weeks. Primary and secondary outcomes will be measured at baseline and after the 12-week intervention period. The participant flow for this trial is presented in Fig. 1. The present protocol follows the Standard Protocol Items: Recommendations for Interventional Trials (SPIRIT) guidelines and fulfills the SPIRIT checklist (see Additional file 1).

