### Sample size calculation

The primary outcome of this trial involves global health-related physical fitness ability changes which are assessed using composite points of health-related physical fitness. According to study data [34], the mean and standard deviation of a composite point in the health-related physical fitness of college students were measured as 55 points and 12.5 points, respectively. A sample size of 100 will have 80% power to detect a difference in a composite score of health-related physical fitness of 5.0% and an α of 0.05 for a two-sided significance level. Assuming a maximum loss to follow-up of 20%, a total of 120 subjects was necessary.

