#### Primary outcome

According to China’s National Student Physical Health Standard (2014 Revision) [36], the health-related physical fitness measurements consist of body mass index (BMI), vital capacity (VC), 50-m running, body anteflexion in sitting position (BAISP), standing long jump (SLJ), pull-ups per minute (male)/sit-ups per minute (female), and 1000-m running (male)/800-m running (female). Overall assessment of health-related physical fitness is evaluated using a composite point which is calculated as the summation of the points of each measurement multiplied by the participant’s corresponding weight. A composite point of health-related physical fitness = 15%BMI points + 15%VC points + 20% 50 m running points + 10% BAISP points + 10% SLJ points + 10% pull-up (male)/sit-up (female) points + 20% 1000 m (male)/800 m (female) running points. The scoring standard and weight of each measurement are listed in Tables 1 and 2.

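### Baseline significance tests choose the covariates of the efficacy model, so adjustment depends on chance and non-significant imbalance in prognostic variables, chiefly the baseline score, stays in the estimate

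*Protocol article*

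**What the plan says.** All of this is in the protocol article.

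- **Baseline testing (Statistical analysis).** "Baseline characteristics between groups will be compared using the" t test or Mann–Whitney test for continuous variables, and chi-squared or Fisher's exact test for categorical ones.
- **Consequence of those tests (same section).** "If incomparability appears, the inequality factors will be treated as confounding variables in the final efficacy analysis". No covariate is named in advance, and the section does not say in what form a flagged factor would enter.
- **Threshold (same section).** None is given for incomparability. The only level stated is the general one: "Statistical significance is defined as a two-sided" P value below 0.05.
- **Treatment effect (same section).** It is to come from "mixed linear models with restricted maximum likelihood using the group-by-time interaction terms". Plain t or non-parametric comparisons at baseline and after the intervention are listed beside it.
- **Allocation (Study design; Randomization, allocation, and blinding).** Students are "randomly allocated to either the Baduanjin exercise group or the control group at a ratio of 1:1", and "The random allocation sequence will be produced by an independent statistician via the PLAN sentences of the statistical software SAS 9.1".
- **Role of sex (Primary outcome; Tables 1 and 2).** The composite uses "pull-ups per minute (male)/sit-ups per minute (female), and 1000-m running (male)/800-m running (female"), and points are read from sex-specific tables.
- **Scale (Sample size calculation).** The composite's mean and SD "were measured as 55 points and 12.5 points, respectively". The target difference is given as 5.0%.

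**The concern.** This is a stated rule, so it cannot be set aside as a detail left to the analysis plan. Under proper randomisation the null hypothesis of a baseline test is true by design. The test therefore carries no information on what an adjustment decision needs, namely how strongly the variable predicts the outcome.

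The rule can err in both directions. It brings in an irrelevant variable that happens to reach significance, and it leaves out a strongly prognostic one that narrowly misses. The model that produces the headline result is then settled only after the data are seen. The variable for which this matters most is the baseline value of the outcome itself, which is measured in everyone.

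**Working it through.** The rule has no figure of its own to reproduce. The document supplies SD 12.5, mean 55, 120 students allocated 1:1 (60 per arm) and a two-sided 0.05 level. The target is 5 points, or 0.05 × 55 = 2.75 points if 5.0% is relative. Assumptions: the 0.05 level governs the baseline tests; equal variances at both visits; a baseline to week-12 correlation r, which the document does not give, shown over a range.

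**1. How often chance alters the model.** For k independent tests, P(at least one significant) = 1 − 0.95^k.
- k = 5: 23%
- k = 10: 40%
- k = 15: 54%

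Entry can also turn on the choice between two permitted tests. With 30 of 60 women in one arm and 41 of 60 in the other, chi-squared gives P = 0.041 and Fisher's test P = 0.063.

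**2. Baseline gap that goes unflagged.** SE = 12.5 × √(2/60) = 2.28 points; 1.96 × 2.28 ≈ 4.5 points.

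**3. What that gap does to the planned contrast.** With two visits and complete data, the group-by-time term is the difference in mean change. Given a chance baseline gap d, the expected week-12 gap without any treatment effect is r × d, so the expected shift is r × d − d = −(1 − r) × d. For d = 4.5:
- r = 0.7: 0.3 × 4.5 = 1.35 points
- r = 0.5: 0.5 × 4.5 = 2.25 points

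The sign is opposite to the gap: an arm that starts higher is penalised.

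**4. Precision forgone.** The variance per student is 2σ²(1 − r) for a change score and σ²(1 − r²) for ANCOVA. The ratio is (1 + r)/2, which is 0.75 at r = 0.5 and 0.85 at r = 0.7.

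**5. Simulation.** 8000 runs, 60 per arm, SD 12.5, effect 5 points (0.4 SD) for power. The last two columns are type I error when the baseline imbalance is sizeable but unflagged (|z| from 1.28 to 1.96).

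| r | Power, change score | Power, ANCOVA | Type I, change score | Type I, ANCOVA |
|---|---|---|---|---|
| 0.3 | 45.4% | 62.5% | 10.0% | 4.8% |
| 0.5 | 57.8% | 70.2% | 8.9% | 5.0% |
| 0.7 | 79.7% | 86.0% | 6.7% | 4.4% |

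Unconditionally, the change score rejects a true null in 5.0% to 5.2% of runs.

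For the plain post-intervention comparison, adjusting only when the baseline test is significant gives power of 59.0%, 58.9% and 60.7% at the same three values of r. Its overall type I error is 4.7%, 4.5% and 3.7%, and its type I error in the unflagged range is 6.4%, 9.4% and 9.8%.

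**6. Sex.** With an assumed 50% men, the SE of the difference in proportion is √(2 × 0.25/60) = 0.0913, so the flagging limit is 1.96 × 0.0913 ≈ 18 percentage points. A split of 30 against 40 women (10/60, or 17 points) gives P = 0.064 by chi-squared and would not be flagged. If the sexes differ by an assumed 2 to 10 composite points, that split moves the week-12 difference by 2 × 10/60 = 0.3 to 10 × 10/60 = 1.7 points. In the group-by-time contrast the same constant difference is subtracted at both visits and the shift is zero.

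**The case against.** The strongest reply is that the plan attaches the treatment effect to the group-by-time term, which already uses the baseline score as a response. Much of what seems alarming then falls away, and three stronger readings are not supported.

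- **That chance imbalance in sex biases the treatment estimate.** A reader might infer this because sex determines the tests carrying 10% + 20% = 30% of the weight. A constant sex difference in level cancels in the contrast, and the sex-specific scoring tables should tend to shrink such a difference. The documents give no size for it. Sex imbalance matters only for the plain post-intervention tests, or if sex affects change over time. That no stratification is described proves nothing, since an article may leave such detail to the full protocol.
- **That an unflagged 4.5-point baseline gap passes into the result almost whole.** Only the fraction (1 − r) does, with reversed sign.
- **That the rule inflates the false-positive rate.** Overall type I error in the simulation is at or below about 5%. The excess appears only conditionally, given an imbalance that was sizeable but unflagged.

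Two further replies have some weight. The statistician works with coded arms until the analysis is finished, which limits steering towards a favourable result; it does not make the model prespecified. And incomparability is never defined as P < 0.05, so the numerical thresholds are an inference. An undefined threshold, however, leaves more discretion.

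Nor does the rule reliably correct what it flags. With complete data, a covariate added only as a main effect leaves the group-by-time estimate unchanged, and a flagged baseline score would stand on both sides of the model.

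**Conclusion.** The point holds as a fault in how the analysis is fixed and should be changed before the data are analysed. It does not make the trial's inference invalid. The rule gives roughly a one-in-four to one-in-two chance (23% to 54%) that chance differences change the model, assuming 5 to 15 independent tests at the 0.05 level.

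For the planned contrast, an unflagged baseline gap at the limit shifts the expected estimate by 1.35 to 2.25 points: 27% to 45% of a 5-point target, or 49% to 82% of a 2.75-point one (1.35/5, 2.25/5, 1.35/2.75, 2.25/2.75). This rests on r between 0.5 and 0.7, equal variances and complete data. A gap that large is the extreme case; smaller gaps scale down in proportion. The more routine loss is precision, since fixed baseline adjustment would have 0.75 to 0.85 of the variance.

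**What to change.** Delete the baseline hypothesis tests and the rule that feeds their results into the efficacy analysis; summarise baseline data by arm descriptively. Prespecify one baseline-adjusted primary analysis, to be used whatever the observed balance:

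- **Either** ANCOVA of the week-12 composite on group, with baseline composite and sex as covariates;
- **or** a mixed model with baseline and week 12 as responses, baseline means constrained equal across arms, and sex with sex-by-time.

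The second fits more easily with the article's commitment to include all randomised students and handle missing data by likelihood, since it retains those with a baseline value only. Baseline must not be both response and covariate, and sex as a main effect alone would do nothing for the group-by-time term. Use the same form for the secondary outcomes. Any further adjustment belongs in a sensitivity analysis.

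The cost is one or two degrees of freedom and a modest rewrite of the model statement. No new data are needed: the baseline outcome is already measured, and sex must be known to score the composite.

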#### Outcome assessment

Outcome measurement of participants will be performed at the campus gymnasium by physical education teachers who do not participate in the implementation of this trial. Primary and secondary outcomes will be assessed at baseline and after the 12-week intervention period.

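### If an unequal baseline factor is entered as an ordinary covariate, it cancels from the two-visit group-by-time effect, so confounding of 12-week change would stay unadjusted

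*Protocol article*

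**What the plan says.** Three statements in the protocol article bear on this.

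- **Remedy for imbalance** (Statistical analysis): after baseline comparisons, "If incomparability appears, the inequality factors will be treated as confounding variables in the final efficacy analysis".
- **Efficacy model** (Statistical analysis): "the between-group differences (treatment effects) will be analyzed by using mixed linear models with restricted maximum likelihood using the group-by-time interaction terms".
- **Visits** (Outcome assessment): "Primary and secondary outcomes will be assessed at baseline and after the 12-week intervention period".

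Two further statements affect how exact the point is. Incomplete cases stay in the model: "Full information maximum likelihood estimation will be employed for missing data". Loss is expected (Sample size calculation): "Assuming a maximum loss to follow-up of 20%, a total of 120 subjects was necessary".

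The article does not say whether an unequal factor enters as a main effect only or also with an interaction with time.

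**The concern.** With two visits, the group-by-time interaction is the between-arm difference in mean change from baseline. A factor that is constant over time (sex, age, school year), entered as a plain covariate, adds the same amount to both of a student's records, so it drops out of that student's change. Yet confounding of change is the only kind that can still affect this effect measure, because effects on level have already been differenced away.

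A statistician who follows the rule in the most natural way could therefore report an effect as adjusted for a confounder when the estimate is the unadjusted one, or nearly so. An imbalance in a factor that predicts 12-week change would remain in the primary estimate. Any precision the factor could add for change would also be lost.

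**Working it through.** **Inputs from the article.** Two visits; effect = group-by-time interaction; 120 students at 1:1, so 60 per arm; composite SD 12.5 (the mean and SD "were measured as 55 points and 12.5 points, respectively"); loss up to 20%. The article gives no figure on this point to reproduce.

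**Inputs assumed.** Correlation between visits 0.4 to 0.8; for the general simulations, a standardised factor unequal by 0.5 SD, with a slope of 4 points at baseline and 4 or 7 at week 12; true effect 5 points.

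**1. Algebra, complete data.** Let x be the factor, Δx its difference in mean between arms, and β its main-effect coefficient. The adjusted contrast between arms is:

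- baseline: D0 − βΔx
- week 12: D1 − βΔx
- interaction: (D1 − βΔx) − (D0 − βΔx) = D1 − D0

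The result does not depend on β or on the 2×2 covariance. With a factor-by-time coefficient γ, the interaction becomes (D1 − D0) − γΔx. So γΔx is the conditional bias that main-effect entry leaves in place.

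**2. Numerical check, complete data.** One simulated trial, REML; results were identical under compound symmetry and unstructured covariance:

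| Model | Interaction (SE) |
|---|---|
| No factor | 9.508 (1.867) |
| Factor as main effect | 9.508 (1.867) |
| Factor plus factor-by-time | 8.864 (1.988) |

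Over 150 replicates with correlation 0.6, true effect 5 and a factor that predicts change (γ = 7 − 4 = 3), the mean estimates were 6.34, 6.34 and 4.81. The last step moves the estimate by 1.53, against γΔx = 3 × 0.5 = 1.5. With γ = 0 all three models agree closely (5.21, 5.21, 5.20).

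**3. With loss at week 12.** The cancellation is no longer exact, because the mean of x among students seen at week 12 can differ from its mean at baseline. With equal variances and correlation ρ, adding the main effect changes each arm's estimated mean change by β(1 − ρ)(mean x of all − mean x of completers). The effect shifts by the difference of this between arms. Simulated absolute shift from adding the main effect, averaged within each scenario:

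| Loss, about 20% | Range of mean shifts (points) |
|---|---|
| Random | 0.06 to 0.22 |
| Depends on the factor, same in both arms | 0.08 to 0.32 |
| Depends on the factor, differently by arm | 0.35 to 1.26 (largest single shift 2.8) |

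The shift corrects for who is missing. It does not remove γΔx: with random loss, correlation 0.6 and γ = 3, the means were 6.83 unadjusted, 6.83 with the main effect and 5.33 with factor-by-time.

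**4. An imbalance that would trigger the rule.** With 37/60 v 25/60 men:

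- chi-squared = 120 × (37×35 − 23×25)² / (60×60×62×58) = 4.81, P = 0.028 without continuity correction
- Δx = 12/60 = 0.20

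| Assumed sex difference in 12-week change (points) | Bias left (points) |
|---|---|
| 0 | 0 |
| 2 | 0.4 |
| 4 | 0.8 |
| 6 | 1.2 |

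In 40 simulated complete-data trials with this imbalance and a 4-point difference, a sex main effect moved the interaction by at most 1.4 × 10⁻¹³ points. Adding sex-by-time moved it by 0.80.

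**5. Baseline composite as the unequal factor.** Entering it as a covariate, while it is also the first response, leaves the complete-data estimate unchanged, so regression to the mean is not removed. The standard error can change: in random-intercept fits it fell on average from 2.05 to about 1.95.

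**The case against.** The strongest objection is that the article never says main effect only. A factor-by-time term fits its wording too, and then the adjustment works. A journal article may leave the form of entry to an analysis plan that is not shown. This stands, and it limits the point to the usual way of following the rule. The point is still more than missing detail: the rule, the effect measure and the two visits are all stated, and the usual way of combining them gives an adjustment that hardly adjusts.

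A reader might infer that the planned adjustment does nothing at all. The documents do not support that, for two reasons. The form of entry is open. And the article expects loss and keeps incomplete cases by likelihood, so the estimate does move. When loss depends on the factor differently by arm, the main effect can be useful: with correlation 0.4 and γ = 0, it moved the mean estimate from 3.87 to 4.85, against a true 5.

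A reader might also infer that no confounding is removed. That is wrong as well: the within-student contrast already removes every constant effect of the factor on level. Only an effect on change is left, and under randomisation the imbalance is due to chance.

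Last, nothing in the article supports any particular sex difference in change. Men and women take different tests for 30% of the composite (10% strength, 20% distance running), but they are scored on separate standards. Different tests do not imply different trends, and the difference may be zero.

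**Conclusion.** The point holds in conditional form. If an unequal factor is entered as a covariate main effect, the complete-data interaction is unchanged, exactly. With loss near 20% it usually shifts by about 0.06 to 0.3 points, and by more if loss depends on the factor differently by arm. A factor that predicts 12-week change stays unadjusted.

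The size is modest. The 0.8-point example is 16% of the target if the 5.0% in Sample size calculation means 5 points, and 29% if it means 5% of 55, which is 2.75 points. With SD 12.5, correlation 0.6 and 60 complete pairs per arm, the standard error of the interaction is √(2 × 2 × 12.5² × 0.4 / 60) = 2.04, so 0.8 points is about 0.4 standard errors. The algebra needs no assumption beyond main-effect entry and complete pairs. The sizes rest on the assumed trend differences, correlations and patterns of loss. This is a cheap improvement worth making, not a flaw that invalidates the analysis.

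**What to change.** In Statistical analysis, state how adjustment factors enter. Either of these would serve:

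- **Keep the mixed model:** each adjustment factor enters together with its interaction with time.
- **Change the estimator:** model the week-12 score with the baseline score and the factors as covariates. This also adjusts for baseline imbalance in the outcome and is generally more precise.

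The two are not equivalent. In the single simulated trial above, the first gave 8.864 (SE 1.988) and the second 8.316 (SE 1.759). One should be named as primary.

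The cost is a sentence of wording, no new data, and about one degree of freedom per added term. The second option needs one more line. A plain week-12 regression uses only students with a week-12 score, so it must be reconciled with the statement that "All participants who have been randomized will be included in the final analysis irrespective of compliance or withdrawal from the program".
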